### Randomization and blinding

2.11

Participants will be randomly assigned to either the intervention group (SMY group) or the placebo control group in a 1:1 ratio using a centralized web-based randomization system. Randomization will be stratified by study center, and the sequence will be computer-generated with permuted blocks of variable sizes within each center to ensure balanced allocation while minimizing predictability. The allocation sequence will remain concealed from participants and study personnel, including physicians, investigators, data collectors, and statisticians, to prevent selection bias.

This trial will be conducted in a double-blind manner, ensuring that both participants and study personnel remain unaware of treatment assignments throughout the trial. To ensure effective blinding, SMY and its placebo will be designed to be indistinguishable in appearance, smell, taste, and packaging.

### Unblinding

2.12

An independent Data Monitoring Committee (DMC) will conduct periodic safety reviews and will have access to unblinded safety data to ensure patient safety and trial integrity. The study investigators and other study personnel will remain blinded unless emergency unblinding is deemed necessary for patient safety. The decision to unblind a participant will be made by the principal investigator or the DMC, based on predefined criteria.

Unblinding will be conducted through the centralized randomization system, which maintains a secure and auditable record of all unblinding requests. In the event of unblinding, the reason, date, and responsible personnel will be documented, and its potential impact on study outcomes will be assessed.

Routine unblinding will not be performed before database lock and statistical analysis. The randomization codes will remain concealed until the completion of data analysis, except for cases of authorized emergency unblinding.

### Interventions

2.13

Participants will receive treatment for 8 weeks. During the treatment period, participants are not allowed to take any other TCM containing components similar to those in SMY.

#### Intervention group (SMY group)

2.13.1

Participants randomized to the intervention group will receive standardized Western medicine treatment in combination with SMY. SMY will be administered orally at a dose of 1 vial, three times daily (1 vial, TID, PO).

#### Placebo control group

2.13.2

Participants randomized to the placebo control group will receive standardized Western medicine treatment in combination with a placebo matched to SMY. The placebo will be identical in appearance, smell, taste, and packaging to SMY, ensuring effective blinding. It will be administered orally at the same dose and frequency as SMY (1 vial, TID, PO).

#### Standardized western medicine treatment

2.13.3

All participants will receive standardized Western medicine treatment individualized to clinical conditions, including:
Physician-determined chemotherapy regimens incorporating anthracyclines (21, 22).Primary prevention of ACT, recommended by clinical guidelines (26), may include dexrazoxane, angiotensin-converting enzyme inhibitors (ACEIs) or angiotensin II receptor blockers (ARBs), β-blockers, and/or statins, tailored to individual patient risk profiles.Guideline-directed therapy for PVCs (23). For most symptomatic patients, β-blockers are the first-line treatment. Other standard options, including antiarrhythmic drugs (AADs) and catheter ablation in selected cases, are permitted as clinically indicated.Medications for hypertension, diabetes, dyslipidemia, and other comorbidities, as clinically indicated.

#### Drug dispensation and retrieval

2.13.4

SMY and its placebo will be dispensed by trained study personnel at each follow-up visit. Participants will be instructed to return all used and unused vials at each follow-up visit, and medication compliance will be assessed through vial counts and participant self-reports. The actual amount of medication taken within the range of 80% to 100% of the prescribed dosage is considered to meet the protocol requirements for medication compliance.

### Outcome measurements

2.14

#### Primary outcome

2.14.1

Percentage reduction in anthracycline-induced frequent PVCs, which is calculated by subtracting the post-treatment 24 h PVC count at 8 weeks from the baseline 24 h PVC count, then dividing the result by the baseline 24 h PVC count, and multiplying by 100%.

#### Secondary outcomes

2.14.2

PVC symptom score at 8 weeks**:** Currently, there is no standardized scale for PVC symptom assessment. Based on expert opinions, we have developed a scale to preliminarily evaluate the impact of anthracycline-induced frequent PVCs on participants and to assess changes in symptom scores before and after SMY treatment. The scoring will be based on patient self-reports and will include the following symptoms: palpitations, dizziness, chest pain, insomnia, and fatigue. Each symptom will be classified into four levels according to its frequency and severity: none, mild, moderate, and severe, corresponding to symptom scores of 0, 1, 2, and 3, respectively.TCM syndrome score at 8 weeks: Based on the diagnostic criteria for QYD syndrome and expert opinions, we have developed the TCM syndrome score, which consider symptom severity as well as tongue and pulse conditions. The detailed scoring criteria are provided in Table 2. Experienced TCM practitioners will assess patients' clinical manifestations and incorporate self-reported symptoms to determine the scores.Cardiac dysfunction biomarkers at 8 weeks: Levels of N-terminal pro-brain natriuretic peptide (NT-proBNP), cardiac troponin I (cTnI), and creatine kinase-MB (CK-MB).Major adverse cardiovascular events (MACEs): Including cardiac death, myocardial infarction, stroke, severe heart failure, and unstable angina requiring hospitalization or revascularization.

#### Safety outcomes and adverse events

2.14.3

Vital Signs: Temperature, blood pressure, respiration, and heart rate.Blood routine test, urine routine test, and stool routine test.Electrocardiogram (ECG), liver function, renal function, and coagulation function, including alanine aminotransferase (ALT), aspartate aminotransferase (AST), total bilirubin (TBIL), direct bilirubin (DBIL), indirect bilirubin (IBIL), blood urea nitrogen (BUN), creatinine (Cr), prothrombin time (PT) and activated partial thromboplastin time (APTT).Adverse events (AEs): Any unfavorable medical event occurring from the time the participant signs the informed consent form until the final follow-up visit, regardless of its causal relationship with the study drug, will be classified as an AE and must be recorded in the CRF. All AEs should be continuously followed up until they disappear or stabilize.

#### Baseline assessments

2.14.4

Baseline data of participants will be recorded before the initiation of treatment:
Demographic information: Gender, age, medical record number, height, weight, smoking history, alcohol consumption history, and study center.Breast cancer or malignant lymphoma information: Pathological classification, breast cancer receptor status, staging, thoracic radiotherapy (laterality and total dose), chemotherapy regimen, cumulative dose of anthracyclines, and primary prevention medications for ACT.Comorbidities and relevant medications: Including hypertension, diabetes, dyslipidemia, coronary artery disease, and cardiomyopathy.TCM diagnostic information: Including diagnostic symptoms, tongue characteristics, and pulse conditions.

#### Other assessments

2.14.5

Tumor progression assessment: Including mammography, breast magnetic resonance imaging (MRI), breast ultrasound, and whole-body contrast-enhanced computed tomography (CT).High-sensitivity predictive biomarker for ACT: Global longitudinal strain (GLS) is one of the most promising indicators of cardiac function assessment after left ventricular ejection fraction (LVEF). Its relative change is an ideal tool for identifying asymptomatic cancer therapy-related cardiac dysfunction (CTRCD) and has greater sensitivity than LVEF (27, 28). Therefore, GLS is selected as the high-sensitivity predictive biomarker for ACT.

### Retention

2.16

Successful completion of evaluation requirements for the study is defined as completing assessments of at least two time periods (baseline and week 8 follow-up). However, participants may withdraw from the study at any time for any reason. Participant retention, termination, withdrawal, and loss to follow-up will be documented and discussed.

### Statistical analysis plan

2.17

Primary efficacy outcome will be analyzed using a linear model (LM). The primary LM model will include the treatment group, study center, and baseline 24 h PVC count. A fully adjusted LM model analysis will also be performed by incorporating pre-specified baseline covariates into the LM model. These covariates include sex, age, BMI, cancer type, thoracic radiotherapy, cumulative dose of anthracyclines, and the presence of any cardiovascular risk factors (hypertension, diabetes, dyslipidemia, coronary artery disease, cardiomyopathy, smoking, and alcohol consumption). The unadjusted and adjusted mean difference between intervention and control in the primary outcome, together with its 95% confidence intervals (CIs) will be derived from the LM models. In addition, subgroup analysis of the primary endpoint will be performed on the pre-specified covariates including baseline 24 h PVC burden which will be examined in quartiles (*Q*1–*Q*4) as a pre-specified subgroup. Treatment heterogeneity will be assessed by fitting a treatment-by-subgroup interaction using a Wald test. Normality assumption for the residuals will be assessed using *Q–Q* plot. The win ratio method will be employed if normality assumption is violated. Missing data will be imputed using the multiple imputation method.

Analysis of secondary continuous outcomes and GLS will be performed in a similar way to the primary outcome analysis. Analysis of secondary binary outcomes will be performed using generalized linear model (GLM) models with binomial distribution and log function. The risk ratio with 95% CIs between intervention and control will be derived from the GLM model.

Exploratory analyses: The associations between (i) baseline TCM syndrome score and baseline 24 h PVC count, and (ii) change in TCM syndrome score and the percentage reduction in PVCs will be assessed. For each association, Spearman's rank correlation will be computed. For (ii), a LM will be fitted in a similar way to the models for continuous outcomes.

Analysis of safety outcomes and AEs: AEs will be summarized as the number of cases and incidence rates, with comparisons made between groups. Abnormalities in vital signs, liver function, renal function, and coagulation function after treatment will be summarized using contingency table, and differences between groups will be analyzed.

All statistical analyses will be performed using SPSS Version 26.0 (IBM Corp, Armonk, NY, USA) and R version 4.1.1. The trial results will be reported following the Consolidated Standards of Reporting Trials (CONSORT) guidelines for reporting randomized trials (29).

Primary data analyses will be based on the intention-to-treat principle. The per-protocol analyses will also be performed as supplemental analysis. Descriptive statistics will be produced for outcome variables and for baseline characteristics of patients by treatment arm. Continuous variables will be summarized using number of observations, mean (SD) or median (IQR) depending on their distributions; categorical variables will be summarized by the number and percentage.

No interim analysis of outcomes is planned. No multiple adjustment will be made.

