### Sample size

2.10

A previous RCT demonstrated that after 4 weeks of treatment, the number of PVCs within 24 h decreased from 15,138 ± 7,597 to 5,686 ± 5,940 in the intervention group. While in the placebo group, the number decreased from 14,529 ± 5,929 to 10,592 ± 8,009 (25). The reduction in PVC counts for both groups was converted into reduction rates, which were 62.44% ± 39.24% in the intervention group and 27.10% ± 55.12% in the placebo group. The standard deviation (SD) of the reduction rate was estimated by dividing the reported post-treatment SD of PVC counts by the baseline mean number of PVCs.

Based on these findings, we assumed that the mean percentage reduction in 24 h PVC counts would be 60% in the intervention group and 35% in the placebo group, with SDs of 39% and 55%, respectively. To detect a between-group difference of 25% in the percentage reduction rate with 95% power at a two-sided significance level of 5%, a total of 95 participants per group would be required. Allowing for a 10% loss to follow-up, the final required sample size was set at 212 participants, with 106 participants allocated to each group.

Each participating center has a high volume of patients. Adequate study personnel will be assigned to screen, monitor, and recruit potential participants to ensure that the target sample size is achieved.

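### The primary effect measure is not fixed: a visual normality check decides between the linear-model mean difference and a win ratio, and the trial is sized only for the former

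*Protocol article*

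**What the plan says.** Section 2.14.1 defines the primary outcome as baseline minus week-8 24 h PVC count, "then dividing the result by the baseline 24 h PVC count, and multiplying by 100" percent. Section 2.17 names the model: "The primary LM model will include the treatment group, study center, and baseline 24 h PVC count". The effect reported from it is a mean difference with a 95% CI.

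The same paragraph adds a condition in two sentences: "Normality assumption for the residuals will be assessed using *Q–Q* plot", and then "The win ratio method will be employed if normality assumption is violated". It gives no cut-off and does not say who reads the plot, or whether the mean difference keeps its primary status once the win ratio is used.

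Section 2.10 sizes the trial for a 25-point difference in mean reduction (60% against 35%), "with SDs of 39% and 55%, respectively". For other endpoints, section 2.17 says: "Analysis of secondary continuous outcomes and GLS will be performed in a similar way to the primary outcome analysis".

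**The concern.** A confirmatory trial should have one primary effect measure, fixed before the outcome data are examined. Here the choice depends on a visual reading of those data, and the two candidates measure different things. One is an average difference in percentage points. The other is the ratio of pairwise comparisons won to those lost by the SMY arm.

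The condition is also likely to be met. A percentage reduction stops at +100%, when no PVCs remain, but can be strongly negative. Section 2.5 admits patients with paired or consecutive PVCs and sets no minimum count for them, so some denominators may be small. Two competent analysts could read the same plot differently and put forward different primary results, and the one put forward may not be the effect for which the trial was sized.

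**Working it through.** **1. The plan's own figure.** Inputs from section 2.10: difference 25, SDs 39 and 55, two-sided 5%, power 95%.
- Pooled SD = √((39² + 55²)/2) = 47.68.
- n per arm = 2 × (1.960 + 1.645)² × 47.68² / 25² = 94.5, so 95.
- 95/0.90 = 105.6, so 106 per arm and 212 in total.

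The stated size is reproduced. It is a calculation for a mean difference.

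**2. The ceiling.** Normal mass above 100% at the planning values:
- SMY: (100 − 60)/39 = 1.03 SD, tail 15.3%.
- Placebo: (100 − 35)/55 = 1.18 SD, tail 11.9%.

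These values cannot occur, so the outcome cannot follow those normal distributions.

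**3. How often the check would fail, and what the rule does to error rates.** The documents give only means and SDs, so the shapes below are assumptions. Each row comes from 5,000 simulated trials per scenario at 95 per arm. Shapiro-Wilk stands in for the Q-Q reading, an unadjusted two-sample t-test for the linear model, and a Mann-Whitney test for the win ratio. Type I error uses the placebo values (35, SD 55) in both arms. Capping alters the planned mean and SD somewhat.

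| Assumed shape | Normality rejected at 0.05 / 0.001 (planned effect) | Power, mean / rank | Type I, mean test | Type I, mechanical switch | Type I, picking whichever is significant |
|---|---|---|---|---|---|
| Gamma post/baseline ratio | 100% / 100% | 95.7% / 96.8% | 5.5% | 4.6% | 7.1% |
| Lognormal post/baseline ratio | 100% / 100% | 95.4% / 99.8% | 4.5% | 4.8% | 7.0% |
| Normal capped at 100% | 99.4% / 66.0% | 98.4% / 94.4% | 5.5% | 5.3% | 6.3% |
| Uncapped normal (not possible here) | 11.1% / 0.6% | 95.1% / 93.9% | 4.9% | 5.0% | 5.8% |

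For the three shapes that respect the ceiling, the two tests disagree on significance in 1.8% to 4.7% of trials. The mean test keeps its planned power and a type I error near 5% under all of them, so the switch is not needed to protect it at this sample size.

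**4. Whether the two measures answer the same question.** Under the planning normals, the win probability is Φ(25/√(39² + 55²)) = Φ(0.371) = 0.645, a win ratio of 0.645/0.355 = 1.81. Across the assumed shapes, the planned effect corresponds to a win ratio of about 1.8 to 2.2.

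Now set the mean reductions equal at 35%, so the mean post/baseline ratio is 65% in both arms. Keep the SDs at 39 and 55 and assume lognormal ratios.
- Log variances: ln(1 + (39/65)²) = 0.307 and ln(1 + (55/65)²) = 0.540.
- Difference in log means = (0.540 − 0.307)/2 = 0.116, with the lower log ratio on placebo.
- SMY win probability = Φ(−0.116/√(0.307 + 0.540)) = Φ(−0.126) = 0.450.
- Win ratio = 0.450/0.550 = 0.82, although the mean difference is 0.

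In 4,000 simulated trials of this case, the mean test rejected in 5% and the rank test in 22%. In two variants (SDs 55 and 80; or mean reduction 50% with SDs 39 and 55) the win ratio was 0.78 and 0.80, and the rank test rejected in 32% and 28%. The mean test stayed between 5% and 6% throughout.

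**The case against.** The fallback is a single method named in advance. Section 2.11 conceals the allocation sequence from statisticians among others, and section 2.12 keeps the codes concealed until data analysis is complete. That limits result-driven choice and it stands, although the protocol does not say that the plot is judged before any coded comparison is run.

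The ceiling calculation uses marginal distributions, whereas the plan checks model residuals. Its SDs are approximations, because section 2.10 obtained them by dividing post-treatment SDs by baseline means. This stands too. A reader might infer that the switch is almost certain to be triggered, but that depends on assumed shapes. Under the mildest, rejection at the 0.001 level fell to 66%, and a reader of a plot could go either way.

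A reader might also infer that the win ratio would lose the center and baseline adjustment, or that the adjusted and subgroup models would stay on the linear-model scale. The article says neither. It is silent on these details, which a full protocol or SAP may settle.

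Extension to the secondary endpoints is a natural reading of the wording on similar analysis, not an explicit statement. The documents give no figures on skew in NT-proBNP, cTnI or CK-MB, so nothing here rests on it.

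None of this removes the central point. A separate SAP could add a criterion for reading the plot, but the effect measure would still depend on the outcome data.

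**Conclusion.** The concern holds as a problem of an unfixed primary estimand. Section 2.17 lets a visual check decide whether the primary result is a mean difference or a win ratio. Non-normal residuals are likely, given a ceiling that the planned normals would exceed in about 15% and 12% of patients. The two measures can diverge: under equal means, the protocol's unequal SDs and an assumed lognormal shape, rejection is about 5% against 22%.

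A reader might infer that the test is invalid or the trial underpowered. The calculations do not support that. With identical arms, the mechanical rule gave 4.6% to 5.3% type I error under the shapes that respect the ceiling. Only picking whichever test is significant raised it, to 6.3% to 7.1%. Under the planned effect, power was about 94% or more for either test. These results rest on the assumed shapes and on unadjusted stand-ins for the planned models. The sample size of 212 is not affected.

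**What to change.** Before unblinding, amend section 2.17 as follows:
- Delete the conditional switch.
- Keep the linear-model mean difference, adjusted for center and baseline 24 h PVC count, as the single primary analysis, with heteroscedasticity-consistent (HC3) or bootstrap CIs and no normality gate. The Q-Q plot can remain as a reported diagnostic.
- Always report a win ratio stratified by center as a sensitivity analysis, whatever the residuals look like.
- Apply the same no-switch rule to the secondary continuous outcomes and GLS.

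An ANCOVA on log counts may be added as a further sensitivity analysis. It should not be required as the primary analysis, because it would itself replace the defined percentage-reduction outcome and the 25-point effect used for sizing.

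The cost is a few sentences and one extra analysis that is always reported.

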### Quality control

2.18

To ensure the quality of this trial, a multicenter trial coordination committee and an overall principal investigator will be established. The coordination committee, consisting of principal investigators and key researchers from each center, will be responsible for addressing issues arising during the trial. All researchers and staff involved in this study will undergo training based on standard operating procedures (SOPs) to ensure a thorough understanding of the trial's objectives and procedures. To reduce inter-center variability in the diagnosis of TCM syndrome and scoring, each site will employ a fixed roster of TCM practitioners. Prior to randomization, all TCM practitioners will complete centralized training. A unified inquiry template and scripted prompts will be used for both diagnosis and scoring to standardize information elicitation across centers. When a replacement is unavoidable, the incoming TCM practitioner will complete the same training before assessing participants. The DMC will appoint inspectors to conduct regular on-site monitoring (no less than once per month) to safeguard participant rights, ensure compliance with the trial protocol, and maintain data accuracy.

The CRFs will be independently entered into the online database by two data collectors, and the data will be reviewed and verified by the DMC before being locked. All information about participants will be anonymized and will be kept confidential. The database will be password-protected and managed by the DMC. Complete data will only be accessible during the data analysis phase by study investigators and statisticians.

SMY (Tong Ren Tang Technologies Co., Ltd.) will be supplied as a single lot (Batch No. 24262304) across all sites. Schisandrol A content will be quantified by High-performance liquid chromatography (HPLC) to meet the pharmacopeial threshold (≥0.25 mg/10 mL) (30). Full quality control strategies are detailed in Supplementary Appendix 1.

Adjustments to the protocol are possible in terms of technical details derived by the pilot testing.

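### The DMC with access to unblinded safety data is also assigned the database, pre-lock data verification and the appointment of site inspectors, with no separation stated

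*Protocol article*

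**What the plan says.** Section 2.11 (Randomization and blinding) describes a double-blind trial, "ensuring that both participants and study personnel remain unaware of treatment assignments throughout the trial".

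Section 2.12 (Unblinding) introduces the committee: "An independent Data Monitoring Committee (DMC) will conduct periodic safety reviews", and it "will have access to unblinded safety data to ensure patient safety and trial integrity". On individual cases, "The decision to unblind a participant will be made by the principal investigator or the DMC". For everyone else the rule is: "The study investigators and other study personnel will remain blinded unless emergency unblinding is deemed necessary for patient safety".

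Section 2.18 (Quality control) gives the DMC three further tasks:

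- Monitoring: "The DMC will appoint inspectors to conduct regular on-site monitoring (no less than once per month").
- Data checking: after double entry by two data collectors, "the data will be reviewed and verified by the DMC before being locked".
- Database: "The database will be password-protected and managed by the DMC".

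The same section separately sets up a coordination committee, made up of principal investigators and key researchers from the centers, to deal with issues arising during the trial.

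**The concern.** A safety committee may see data by arm because it stands outside the conduct of the trial. Those who run the database, check records before lock and direct monitoring work inside it, and are normally kept from any knowledge of allocation. Sections 2.12 and 2.18 put both roles in one body.

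Two things are at stake. The first is the protection of outcome data between entry and lock: if people who know allocation also review those data, a checking decision could be influenced by arm, even without intent. The second is the committee's independence: a body that manages the database and appoints the inspectors cannot also stand apart from the quality of that work.

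The trial is particularly exposed to this criticism because the Introduction justifies it by the unreported randomization, allocation concealment and blinding of earlier studies. In addition, two of its secondary outcomes, the PVC symptom score and the TCM syndrome score, are described in the Discussion as unvalidated.

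**Working it through.** No arithmetic applies, so the check sets the sections side by side.

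| Question | Section | What the text gives |
|---|---|---|
| Who may see unblinded data? | 2.12 | The DMC, for safety data |
| Who must stay blinded? | 2.11, 2.12 | Participants, investigators, other study personnel |
| Who manages the database? | 2.18 | The DMC |
| Who reviews and verifies before lock? | 2.18 | The DMC |
| Who appoints the on-site inspectors? | 2.18 | The DMC |
| Who makes corrections, resolves queries or decides the lock? | – | Not stated |
| Is any part of the DMC kept from the unblinded data? | – | Not stated |

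**Step 1. Is it one body?** The abbreviation is defined once, in 2.12, as Data Monitoring Committee. Section 2.18 uses it without redefinition. On the text, it is one body.

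**Step 2. Is there a direct contradiction with the blinding statements?** No. Section 2.12 names the DMC first and then states that investigators and other study personnel stay blinded. The DMC's access is therefore an exception that the plan itself provides for. The problem is the combination of duties.

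**Step 3. What would have to be true for bias to follow?** Three conditions:

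1. The unblinded safety data can be tied to individual participants, or otherwise matched to database records.
2. The people who see those data are also the people who handle the database or the verification.
3. That handling leaves room for judgment over outcome values.

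The article states none of these and rules out none. If the first two hold, arm could be linked to outcome before lock, because the database holding the outcomes is managed by the same body.

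**Step 4. Where in the data flow is the exposure?** It comes after scoring. Holter counts, self-reported symptoms and practitioner scores are generated at the sites, where personnel are to be blinded, and CRFs are then entered twice independently. What remains is the interval from entry to lock, together with the direction of monitoring.

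**Step 5. Can the effect be sized?** No. The database covers all 212 planned participants, but that describes reach and is no measure of bias.

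**The case against.** The strongest reply is that the plan keeps real safeguards. The DMC's stated access is to safety data only. Section 2.17 plans no interim analysis of outcomes. The codes sit in a centralized system with an auditable record of unblinding requests, and are to stay concealed until the analysis is complete, apart from authorized emergencies. Assessors are to be blinded, the primary outcome is a Holter count, and entry is done twice. All of this stands, and it narrows the route to bias.

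A reader might infer that the double-blind is broken, or that 2.18 contradicts the promise in 2.12 that study personnel stay blinded. The documents support neither. Section 2.12 sets the DMC apart from study personnel, and nothing says that participants, assessors, inspectors or site staff learn allocation. The inspectors are appointed by the DMC, but are not said to be members or to receive its reports. A reader might also infer that unblinded people will edit outcomes, settle queries or decide the lock. The text says only that the DMC manages the database and reviews and verifies the data; it gives the DMC no editing, query or lock decision and no efficacy results by arm.

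It can also be said that reporting routes and database permissions belong in a DMC charter or data-management plan, which a condensed article need not reproduce. That is fair for details left out. It does not answer this point, which rests on duties that the article positively assigns.

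Finally, DMC in 2.18 may loosely mean a data-management group. If so, the defect is one of naming, but the published text still has to change.

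**Conclusion.** The concern holds as a conflict of assigned duties. On the published wording, the body entitled to unblinded safety data also manages the database, verifies it before lock and appoints the inspectors, and no separation within that body is stated. This weakens the DMC's independence and the protection of outcome data before lock. It should be corrected.

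The conclusion does not extend to a demonstrated loss of blinding or to a bias of any stated size. It assumes that DMC denotes the same committee in 2.12 and 2.18, which is how the article defines it. The sample size does not depend on this issue.

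**What to change.** In 2.18, assign database management, pre-lock verification and appointment of monitors to data-management and monitoring staff who have no access to allocation and are not the site investigators. In 2.12, limit the DMC to periodic safety review and state that it has no role in data handling before lock.

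These duties should not go to the coordination committee. It consists of site principal investigators and key researchers, who would then oversee the monitoring and data of their own centers.

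If 2.18 already means a different, blinded data-management group, give that group its own name and state that it has no access to the unblinded safety data.

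The cost is a small reassignment of duties and revised wording in 2.12 and 2.18. Participant numbers, visits and the planned analyses do not change.
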